### Randomization

Patients who meet the inclusion criteria will be informed about the study by their orthopaedic surgeon at the department of Orthopaedics of Martini Hospital Groningen (Fig. 1). Patients will be informed about the treatment, the risk of complications according to the Dutch Medical Treatment Contracts Act.

**Fig. 1 Fig1:**
[figure not shown]
Flowchart of patient inclusion

A random allocation set of the type of ACL reconstruction technique will be generated by means of a computer. These allocations are then sealed in consecutively numbered opaque envelopes. Once the patient has given consent to be included in the trial, the ACL reconstruction technique is then randomly assigned by opening the next sealed envelope.

Patients will be blinded for the allocated surgical technique. Measurements and data-analysis will be performed by an independent investigator.

### Data collection methods

MRI images will be obtained one year postoperatively. The current protocol for ACL assessment with MRI will be conducted with the following sequences: sagittal PDWI; coronal PDWI and sagittal PDWI SPAIR fat-suppression (SPectral Attenuated Inversion Recovery) sequence. Besides the normal knee MRI protocol, also gradient echo sequence T2*WI will be obtained by MRI by the following imaging protocol: Pulse sequence, gradient echo; repetition time (TR)/echo time (TE), 500/18 ms; slice thickness/intersection gap 4.0/1.0 mm; field of view (FOV), 15 cm (Table 1). All MRI assessments of the knee are performed on 1.5 T Philips Ingenia MRI (Philips, Best, the Netherlands) with the use a 16 elements knee coil. MRI images of the ACL graft will be analysed a radiologist. It is not possible to blind the radiologist for the allocated surgical technique since it is possible to distinguish these techniques on MRI images. Regions of interests (ROI) will be set manually on the ACL grafts with the PCL serving as control. Mean SI of the ROI for both the ACL graft and PCL will be measured. Hereafter, SIR will be calculated by:

**Table 1 Tab1:** Imaging parameters

	Current knee MRI protocol		Additional MRI protocol
	PDWI	PDWI SPAIR	T2*WI
TR (ms)	1800	3310	500
TE (ms)	200	20	18
Slice thickness (mm)	3.0	3.0	4.0
Intersection gap (mm)	0.3	0.3	1.0
FOV (cm)	15	15	15

*PDWI* proton density weighted imaging, *SPAIR* SPectral Attenuated Inversion Recovery, *T2*WI* T2*-weighted imaging, *TR* repetition time, *TE* echo time, *FOV* field of view

$$ \mathrm{SIR} = \mathrm{A}\mathrm{C}\mathrm{L}\ \mathrm{graft}\ \mathrm{S}\mathrm{I}\ /\ \mathrm{P}\mathrm{C}\mathrm{L}\ \mathrm{S}\mathrm{I}. $$

Each SIR measurement will be repeated three times for intraobserver variation analysis and calculation of mean values. Patients will have regular follow-up with outpatient clinic appointments. Additional outpatient clinic appointment preoperatively and one year postoperatively will be conducted to assess the clinical, functional and patient-oriented outcomes of the ACL reconstruction be means of standardized physical examination, recorded by IKDC examination form and KOOS assessment. These assessments will be obtained by an independent investigator.

### Sample size calculation

Hakozaki et al. assessed the SIR of the double-bundle ACL graft 12 months after ACL reconstruction with the AMP technique [12]. On MRI, the SIR of the graft 12 months postoperative was measured of 61 patients. The mean SIR of the ACL graft was significantly higher (*p* = 0.014) in patients with positive pivot-shift test (SIR = 1.46) than in patients with negative pivot shift test (SIR = 1.25). In the present study, a difference of 20 % was considered clinically relevant. Hence, to detect a difference of 0.25 in SI (SD 0.21) with a power of 90 % and an alpha of 5 %, a sample size of 15 patients in each study group is required. To compensate for potential loss to follow-up of 20 %, the total sample size is set at 36 patients.

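### The SD of 0.21 behind the 90% power is unsourced and equals the cited difference in means; for many group splits the cited p-value implies a larger SD and lower power

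*Protocol article*

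**What the plan says.** The section on sample size in the protocol article rests on one earlier study. It reports 61 patients, mean SIR 1.46 in those with a positive pivot-shift test, 1.25 in those with a negative one, and p = 0.014. It gives neither the number of patients in each pivot-shift group nor any standard deviation from that study, and it does not name the test behind the p-value.

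The protocol then sets its target: "In the present study, a difference of 20 % was considered clinically relevant". From this it plans "to detect a difference of 0.25 in SI (SD 0.21) with a power of" 90% and an alpha of 5%, and concludes that "a sample size of 15 patients in each study group is required". The total is set at 36 to allow for 20% loss to follow-up. Under Statistical analysis, SIR is compared between the groups by t-test or Mann–Whitney test. This is the only comparison that is powered.

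**The concern.** The 0.25 can be traced: it is 20% of 1.25. The SD cannot. The only figure in the section that yields 0.21 is the difference between the two quoted means, and the match is exact to two decimals. A difference in means says nothing about the spread between patients, so if it was entered as the SD, the 90% has no basis.

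The section also quotes a p-value and a total number of patients, and these limit what the SD in the cited study can have been. For many ways of splitting the 61 patients, that SD is clearly larger than 0.21. The SD is the decisive input to the primary comparison. If it is too small, a non-significant SIR result would be read, on the strength of a claimed 90% power, as evidence that the two techniques do not differ.

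**Working it through.** **Inputs, all from the sample size section.** Target difference 0.25; SD 0.21; power 90%; alpha 5% (taken as two-sided); 15 per group; 36 in total, so 18 per arm. Cited study: 61 patients, means 1.46 and 1.25, p = 0.014. The group split is not given, so it is varied below.

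**Step 1. Reproduce the plan's figure.** Normal approximation: n per group = 2 × [0.21 × (1.960 + 1.282) / 0.25]² = 14.83, rounded up to 15. The stated number follows from the stated inputs. At 15 per group the power is 90.3% by the normal approximation and 88.2% by the noncentral t, so the formula is not at fault.

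**Step 2. Compare the SD with the cited means.** 1.46 − 1.25 = 0.21.

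**Step 3. Back-calculate the SD from the p-value (two-sided pooled t-test).** With 59 degrees of freedom, p = 0.014 corresponds to t = 2.533. The standard error is 0.21 / 2.533 = 0.0829, and SD = 0.0829 / √(1/n₁ + 1/n₂) with n₁ + n₂ = 61. Power is for a difference of 0.25 by the noncentral t, at the unrounded SD.

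| Split | Implied SD | Power, 15 per arm | Power, 18 per arm |
|---|---|---|---|
| 6 / 55 | 0.193 | 93% | 97% |
| 7 / 54 | 0.206 | 89% | 94% |
| 8 / 53 | 0.219 | 86% | 92% |
| 10 / 51 | 0.240 | 79% | 86% |
| 15 / 46 | 0.279 | 66% | 74% |
| 20 / 41 | 0.304 | 58% | 67% |
| 30 / 31 | 0.324 | 53% | 61% |

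The implied SD passes 0.21 between 7 and 8 patients in the smaller group. Rounding of the two means (a true difference anywhere from 0.20 to 0.22) moves the SD by about 5% and the crossover by about one patient. If the cited p-value were one-sided, the SDs would be larger: 0.246 at 8 / 53 and 0.364 at 30 / 31.

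**Step 4. Repeat with Welch's test, equal SDs in both groups.** At 10 / 51 the Welch degrees of freedom are about 12.8, so t = 2.844. The standard error is 0.21 / 2.844 = 0.0738, and the SD is 0.0738 / √(1/10 + 1/51) = 0.0738 / 0.3458 = 0.213. A group of about 10 therefore still agrees with 0.21. At 15 / 46 (about 23.8 degrees of freedom, t = 2.652) the standard error is 0.0792 and the SD is 0.0792 / 0.2973 = 0.266, again above 0.21.

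**Step 5. Detectable difference.** With 15 per arm, 90% power by the noncentral t needs a difference of 1.23 SD. That is 1.23 × 0.28 = 0.34 at an SD of 0.28 and 1.23 × 0.32 = 0.39 at an SD of 0.32, against the target of 0.25.

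**The case against.** The strongest reply is that nothing here is shown to be wrong. The arithmetic reproduces, the cited study may itself report an SD of 0.21, and a journal article need not give the origin of every input. Counting splits is also weak evidence, because splits are not equally likely. The Discussion treats a returning pivot shift as a sign of failure, so a small positive group at 12 months is plausible. With 7 positives the protocol's SD fits the pooled test, with 6 or fewer it is conservative, and under Welch it fits up to about 10. Power figures at 15 per arm also assume that all the planned attrition occurs.

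Most of this stands, and it limits the claim. The mix-up is an inference from a numerical match. The crossover depends on the test assumed. The power figures are conditional on a split the protocol does not give, which is why the 18-per-arm figures stand beside the 15-per-arm ones. Full retention does not restore 90% power, though, once the smaller group reaches 10 under the pooled test (86%). Nor is the point only a missing citation: the section states a definite SD and power, and prints figures that agree with them only if one group was small.

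Two stronger readings are tempting. A reader might infer that the trial is shown to be underpowered; without the split or the cited study's SD, it is not. A reader might also infer that 0.25 is an error because it exceeds the whole cited contrast of 0.21. The protocol presents 0.25 as a clinically relevant difference (20% of 1.25), not as the expected effect, and that is a legitimate basis for a sample size.

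**Conclusion.** The point holds as a probably misidentified SD with conditional consequences. The SD of 0.21 has no stated source and coincides with the difference in means. The quoted p-value supports it only if the smaller pivot-shift group had about 7 or fewer of the 61 patients (pooled t-test) or about 10 or fewer (Welch). The 90% power is therefore not supported by the data the protocol quotes.

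If the smaller group had 15 to 30 patients, power for 0.25 is 66% down to 53% with 15 per arm, and 74% down to 61% with all 36 patients retained. These figures assume a two-sided pooled t-test with equal variances in the cited study, and the same SD in this trial. If 0.21 proves to be the within-group SD in that study, the concern falls away once the source is stated. The step from the stated inputs to 15 per group is correct.

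**What to change.** Check 0.21 against the within-group SD in the cited study. If it is that SD, say so in the sample size section. If it is the difference in means, replace it with the reported SD. If none is reported, use the SD back-calculated from that study's p-value and group sizes; the group sizes must come from the cited study, because the protocol does not give them. Then restate, for the planned 36 patients, either the power for a difference of 0.25 or the difference detectable with 90% power (1.23 SD at 15 per arm). The target of 0.25 can stay.

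The cost is one rewritten paragraph and, if the SD turns out larger, a less favourable stated power. No change in enrolment is needed.

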**Methods/design:**

Thirty-six patients will be included in a randomized controlled trial. Patients who are admitted for primary unilateral ACL reconstruction will be included in the study. Exclusion criteria are a history of previous surgery on the ipsilateral knee, re-rupture of the ipsilateral ACL graft, associated ligamentous injuries or meniscal tear of the ipsilateral knee, unhealthy contralateral knee, contra-indications for MRI and a preference for one of the two surgical techniques and/or orthopaedic surgeon. Primary outcome is MRI Signal intensity ratio (SIR) of the ACL graft. Secondary outcome measures are the International Knee Documentation Committee (IKDC) Knee Examination Form,the Knee injury and Osteoarthritis Outcome Scores (KOOS) and the Anterior Cruciate Ligament OsteoArthritis Score (ACLOAS). Differences between MRI SIR assessment with the current MRI protocol (proton density weighted imaging protocol) and the additional T2*-weighted gradient-echo protocol will be assessed.

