### Statistical analysis

All statistical analysis will be computed using SPSS (IBM SPSS, Inc., Version 22.0, 2014). Student’s *t*-test (in case of normal distribution) or Mann–Whitney *U* test (in case of non-normal distribution) will be used to assess the differences in SIR between the study and control group. To assess the differences in outcomes of the IKDC examination form between the study and control group, Chi-square test will be used. Student’s *t*-test (in case of normal distribution) or Mann–Whitney *U* test (in case of non-normal distribution) will be used to compare the outcomes of the KOOS assessments between the study and control group.

Linear regression analyses will be performed to assess whether there is a relation between SI with both MRI protocols (PDWI/PDWI SPAIR and T2*WI) and IKDC score. Linear regression analyses will also be performed to assess whether there is a relation between SIR with both MRI protocols (PDWI/PDWI SPAIR and T2*WI) and KOOS score.

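### Thirty-six patients do not leave 15 per group after the stated 20% loss, and 15 per group gives 88% rather than 90% power for the planned t-test

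*Protocol article*

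**What the plan says.** The whole derivation is in one paragraph of the protocol article, under Sample size calculation. The inputs are a difference of 0.25 in the signal intensity measure and an SD of 0.21, "with a power of 90 % and an alpha of 5" percent. From these the article concludes that "a sample size of 15 patients in each study group is required", which is 30 evaluable patients. It then adds an allowance, "To compensate for potential loss to follow-up of 20" percent, and on that basis "the total sample size is set at 36 patients". The Methods/design part of the abstract repeats the total: "Thirty-six patients will be included in a randomized controlled trial".

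The Statistical analysis section compares the signal intensity ratio between groups with Student's t-test, or with the Mann–Whitney U test if the data are not normal. Under Data collection methods, the MRI that supplies the primary outcome is taken once, one year after surgery. A patient lost before then has no observed primary outcome.

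**The concern.** Two steps in the paragraph look wrong, and both err towards too few patients.

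First, 36 is exactly 30 × 1.20. An allowance for loss has to be divided out, because the loss is a share of the patients enrolled and not of the patients needed. If 15 per group are required and 20% are lost, 36 cannot be enough.

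Second, 15 per group is what the normal-approximation formula returns. That formula treats the SD as known. The planned t-test estimates it, and with groups this small the difference costs about two points of power.

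At stake is whether the stated power can be relied on. A reader would take from the paragraph that the trial keeps 90% power even if one patient in five has no one-year MRI.

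**Working it through.** **Inputs** (all from Sample size calculation unless noted)

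- Difference δ = 0.25; SD σ = 0.21; standardised effect 0.25/0.21 = 1.19.
- Power 90%; alpha 5%. The article does not say whether alpha is one- or two-sided. I take it as two-sided because that reproduces the stated 15.
- Evaluable requirement 15 per group, 30 in total; loss 20%; total 36. I take 36 as 18 per group.
- Primary test: t-test, or Mann–Whitney (Statistical analysis section).

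**Step 1: reproduce the 15 per group.** Normal approximation:

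n = 2 × (1.960 + 1.2816)² × (0.21/0.25)² = 14.83, rounded up to **15**.

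Under that same formula, power at 15 per group is 90.3%. So 15 is reproduced. The one-sided version, with 1.645 in place of 1.960, gives 12.09, so 13, which does not match.

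**Step 2: the loss allowance.**

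- As stated: 30 × 1.20 = 36.
- What remains after a 20% loss: 36 × 0.80 = 28.8, or 14.4 per group, below the required 15.
- Correct inflation: 30/0.80 = 37.5, so **38** (15/0.80 = 18.75, so 19 per group).
- Loss that 36 can absorb: 1 − 30/36 = **16.7%**, or 6 patients.

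This step needs no assumption about the test, its sidedness or the distribution.

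**Step 3: power of the planned t-test.** Two-sided 5%, noncentral t with n₁ + n₂ − 2 degrees of freedom and noncentrality (δ/σ)/√(1/n₁ + 1/n₂). At 15 per group, for example, the noncentrality is 1.19/√(2/15) = 3.26 on 28 degrees of freedom.

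| Evaluable patients per group | Power, t-test | Power, normal approximation |
|---|---|---|
| 14 and 14 | 85.8% | 88.3% |
| 14 and 15 | 87.0% | – |
| 14.4 and 14.4 (36 less exactly 20%) | 86.8% | 89.1% |
| 15 and 15 | 88.2% | 90.3% |
| 16 and 16 | 90.3% | 92.0% |
| 18 and 18 (no loss) | 93.4% | 94.6% |

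The t-test first reaches 90% at 16 per group. If the Mann–Whitney test is used instead, and its relative efficiency is taken as 3/π (an assumption that applies to normal data), power at 15 per group is about 86.6%.

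**Step 4: both steps together.** Sizing for the t-test and dividing for loss gives 16/0.80 = 20 per group, **40** in total.

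**The case against.** The strongest reply has four parts.

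- *Fifteen is not an arithmetic error.* The article names no formula, the normal approximation is standard, and it returns 15. This stands as far as it goes: 15 follows from a choice of method, and 88.2% is close to 90%. On that formula alone the corrected total is 38, not 40. But the formula does not rescue the stated total, because after the stated loss it gives 89.1%, still under target.
- *The shortfall is conditional.* The loss is described as potential. With 4 losses split evenly (16 per group) t-test power is still 90.3%, and with no loss it is 93.4%. This is true and should be said. The allowance exists, however, to protect power when the planned loss occurs, and in that case it does not.
- *The gap is smaller than the uncertainty in the SD.* If the SD were 0.20, 14 and 15 patients would give 90.0%; if it were 0.22, even 16 per group would give only 87.5%. These SDs are assumed for illustration. The point is fair on practical weight, but it does not make the stated figures agree with one another.
- *The hypothesis is directional.* A one-sided 5% test would have 92.2% power at 14 per group. But no one-sided test is stated, and a one-sided calculation gives 13, not 15.

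What stands is that the effect is small, that neither step is large taken alone (36 against 38 patients; 88.2% against 90%), and that the design remains viable.

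**Conclusion.** The concern holds. On the article's own inputs, 36 patients do not leave 15 per group after a 20% loss; they leave 28.8 in total and can absorb 16.7%. This is an inconsistency within one paragraph and rests on no outside assumption.

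For the planned t-test, 15 per group gives 88.2% power. After the stated loss, power is 85.8% to 87.0%, about 3 to 4 points below the stated 90%. These figures assume a two-sided 5% test, normal data with a common SD of 0.21, and near-equal groups.

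The shortfall is modest and does not put the design in doubt. What is wrong is the statement of size and power, which would otherwise be carried into the trial report.

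**What to change.** Correct the Sample size calculation paragraph in one of these ways, and state that alpha is two-sided and which test or formula was used:

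1. Keep 36 and 20% loss, and state about 29 evaluable patients and about 87% power for the t-test.
2. Keep 36 and 15 per group, and state that this tolerates at most 16.7% loss (6 patients) and gives 88% power for the t-test.
3. Keep 90% power and 20% loss, and set the total at 40 (16 evaluable per group). If the normal approximation is deliberately retained, the consistent total is 38, and the text should say that the power is approximate.

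Options 1 and 2 cost one corrected sentence and a slightly lower stated power; design and analysis do not change. Option 3 costs 4 more patients (2 more if 38 is chosen) and a matching change to the total in the abstract.

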### Statistical analysis

All statistical analysis will be computed using SPSS (IBM SPSS, Inc., Version 22.0, 2014). Student’s *t*-test (in case of normal distribution) or Mann–Whitney *U* test (in case of non-normal distribution) will be used to assess the differences in SIR between the study and control group. To assess the differences in outcomes of the IKDC examination form between the study and control group, Chi-square test will be used. Student’s *t*-test (in case of normal distribution) or Mann–Whitney *U* test (in case of non-normal distribution) will be used to compare the outcomes of the KOOS assessments between the study and control group.

Linear regression analyses will be performed to assess whether there is a relation between SI with both MRI protocols (PDWI/PDWI SPAIR and T2*WI) and IKDC score. Linear regression analyses will also be performed to assess whether there is a relation between SIR with both MRI protocols (PDWI/PDWI SPAIR and T2*WI) and KOOS score.

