### Secondary study parameters/endpoints

Differences in functional and clinical outcomes between the AMP and TT ACL reconstruction technique will be assessed by means of the standardized physical examination and recorded by the use of the International Knee Documentation Committee (IKDC) Knee Examination Form [13]. The examination consist of Effusion, Passive Motion Deficit, Ligament Examination (Lachman and Pivot Shift), Compartmental Findings, Harvest Site Pathology and Functional Test (one leg hop test). Laxity measurements will be performed by using KT-2000 arthrometer testing (MedMetric, San Diego, CA). Power measurements of quadriceps and hamstring muscle groups will be performed by using Cybex isokinetic dynamometer (HUMAC). Patient’s will be classified in four groups depending on the lowest grade of the examination form.

Differences in patient-oriented outcomes between the AMP and TT ACL reconstruction technique will be assessed by the use of the Knee injury and Osteoarthritis Outcome Score (KOOS). The KOOS is a knee-specific instrument to assess the patients’ opinion in five subscales of Pain, other Symptoms, Function in daily living (ADL), Function in Sport and Recreation (Sport/Rec) and knee-related Quality of Life (QOL) with scores ranging from 0 (worst) to 100 (best) [14].

Besides differences between MRI SIR assessment with the current MRI protocol (PDWI and PDWI SPAIR imaging protocol) and the additional T2*WI gradient echo protocol. Integrity of cartilage, menisci, bone and other ligamentous structures will be assessed by using the Anterior Cruciate Ligament OsteoArthritis Score (ACLOAS) [15, 16].

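### The ordered four-grade IKDC result is compared with an unqualified chi-square test on about 30 patients, which ignores the grade order and gives up power for a directional shift

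*Protocol article*

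**What the plan says.** The section on secondary study parameters says that patients are "classified in four groups depending on the lowest grade of the examination form". A lowest grade exists only on a ranked scale, so the ordering comes from the article itself.

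The statistical analysis section then states: "To assess the differences in outcomes of the IKDC examination form between the study and control group, Chi-square test will be used". It names no trend, rank or exact version and no pooling of grades. The same section names Mann-Whitney as the non-normal fallback for SIR and KOOS, and relates MRI signal to an IKDC score by linear regression. IKDC is therefore treated as graded in one analysis and as unordered categories in the other.

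On numbers, the sample size section says "a sample size of 15 patients in each study group is required" and, after allowance for loss to follow-up, "the total sample size is set at 36 patients".

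**The concern.** The Discussion asks whether the anatomical technique gives superior functional results, which is a question of direction. A Pearson chi-square on a 2 x 4 table spends 3 degrees of freedom on any departure from equality and makes no use of the fact that one grade is better than the next. With 15 patients per arm, the common condition for the chi-square approximation (expected counts of at least 5) is also hard to meet.

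At stake is a secondary comparison of clinical function in which a real shift between techniques becomes more likely to be reported as no difference. The Background already concedes that clinical assessments need many patients to separate the two techniques, so there is little power to spare.

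**Working it through.** **Inputs.** From the Protocol article: four grades; 15 evaluable per arm; 36 enrolled (18 per arm, assuming 1:1); 20% loss; for the primary outcome SIR, difference 0.25, SD 0.21, power 90%, alpha 5% (two-sided assumed). Not in the article, hence assumed: the IKDC grade distribution and the size of any shift.

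**The plan's own figure.** n per arm = 2 × (1.960 + 1.282)² × 0.21² / 0.25² = 14.8, so 15, as stated. 30 × 1.2 = 36, as stated. With 20% loss, 36 × 0.8 = 28.8, so about 29-30 patients are evaluable. This calculation concerns SIR only; no power is stated for IKDC.

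**Expected counts.** With equal arms of n, the four expected counts in each row sum to n.
- n = 15: mean 15/4 = 3.75.
- n = 18 (no loss at all): mean 18/4 = 4.5.
- All four can reach 5 only if n ≥ 4 × 5 = 20.

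So if all four grades occur, at least one grade, hence two of the eight cells, is below 5 whatever the distribution. If one grade is empty, the mean at n = 15 is 15/3 = 5, and the condition holds only with exactly 10 patients in each remaining grade. In simulation, about 99-100% of tables had a non-empty cell below 5. On average 55-80% of non-empty cells were below 5 at 15 per arm, and 48-69% at 18 per arm.

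**Type I error and power.** 6,000 simulated trials per scenario, 15 per arm, proportional-odds shifts, two-sided 5%. Pearson chi-square (empty grades dropped) against tie-corrected Mann-Whitney; each entry is chi-square / Mann-Whitney rejection rate in %.

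| Assumed grades in one arm (%) | No difference | OR 3 | OR 5 | OR 8 |
|---|---|---|---|---|
| 25/25/25/25 | 4.6 / 5.2 | 22.6 / 35.9 | 43.1 / 63.2 | 65.2 / 82.2 |
| 20/45/25/10 | 4.3 / 4.8 | 20.1 / 35.4 | 40.3 / 61.4 | 64.4 / 81.2 |
| 40/40/15/5 | 3.9 / 4.8 | 18.8 / 32.1 | 37.7 / 57.2 | 54.8 / 75.2 |
| 10/30/40/20 | 4.7 / 5.0 | 20.4 / 34.9 | 43.0 / 64.4 | 67.2 / 84.4 |

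Repeat runs, some with other assumed distributions, widen the ranges to 18-23% against 32-37% at OR 3 and 36-44% against 56-64% at OR 5. With 18 per arm and OR 5, power is 45-53% against 64-73%. The gain in the scenarios run at 15 and 18 per arm is about 13 to 22 percentage points.

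**Cross-check on degrees of freedom alone.** With the noncentral chi-square, a shift that has 80% power on 1 df has about 64% on 3 df, equivalent to needing about 39% more patients.

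**Where the ranking changes.** For an assumed non-monotone difference (25/45/22/8 against 5/75/12/8), chi-square had 29-31% power and the rank test 7-8%. With only three grades in use (33/40/27, OR 3), the gap narrowed to about 27% against 33%.

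**The case against.** The strongest reply is that the chi-square test does no harm to the trial's main result, holds its level, and is not always the weaker test. Much of that stands.

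- A reader might infer from the small expected counts that the test is invalid or produces false positives. The simulations do not support this: type I error stayed at about 3-5%.
- A reader might also infer that the expected-count condition must fail. That follows only if all four grades occur. Under two assumed distributions one grade was empty in 9-44% of simulated tables, and then the condition can be met, though only just.
- A reader might take IKDC to be the main clinical outcome. The article does not rank it so. It is one of several secondary measures, beside KOOS and ACLOAS, with laxity and strength testing also listed. The primary outcome is SIR.
- The power figures depend on assumed proportional-odds shifts, the pattern that most favours a rank test.
- Even after the change, power at an odds ratio of 3 is only about one third, so such a shift would usually be missed with either test.
- That the sentence names no effect estimate is not a fault to raise here, since an article commonly leaves such reporting to the full plan.

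What remains is efficiency. The article commits to a named test, its own definition of the outcome is ordered, and its functional question is directional. For that question the ordered test was better in every proportional-odds scenario run.

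**Conclusion.** The point holds as an inexpensive improvement to one secondary analysis. Ignoring the grade order costs roughly 13 to 22 percentage points of power for a directional shift in the four-grade scenarios run, and less if only three grades are used. It does not make the IKDC test invalid, and it leaves the primary SIR comparison and the sample size untouched.

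The expected-count statement needs only the article's numbers, equal arms and all four grades in use. The size of the power loss rests on assumed grade distributions and proportional-odds shifts, because the article gives neither a distribution nor a target effect. Two small cautions apply to the gap. Chi-square ran slightly below its nominal level, which accounts for a little of it. The rank-test figures are for the tie-corrected normal version; the exact version was not simulated and may be slightly more conservative with tied grades.

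**What to change.** In the statistical analysis section, replace the chi-square sentence for IKDC with one stating that the overall grade, in its four ordered groups, will be compared between the TT and AMP groups by an exact Mann-Whitney (Wilcoxon) test that allows for ties. Show the grade-by-arm table beside the p-value, so that a non-monotone pattern can be seen.

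The cost is one sentence and no new data. The downside is lower sensitivity to non-monotone differences, as the reversed example shows; this is acceptable if a shift towards better or worse grades is the question. A proportional-odds model adjusted for preoperative grade is a doubtful substitute with about 30 patients, because it meets the same sparse cells. The change should be fixed before the data are analysed, so that the test is not switched after small expected counts have been seen.

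### KOOS is measured before surgery and at one year, but the planned arm comparison names no adjustment for the preoperative score and so may give up precision

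*Protocol article*

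**What the plan says.** Secondary study parameters/endpoints makes KOOS a secondary outcome with five subscales, each scored from 0 to 100.

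Data collection methods sets two measurement times: "Additional outpatient clinic appointment preoperatively and one year postoperatively will be conducted to assess the clinical, functional and patient-oriented outcomes", with results "recorded by IKDC examination form and KOOS assessment".

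Statistical analysis gives Student's t-test for normally distributed data and the Mann–Whitney U test otherwise; these serve "to compare the outcomes of the KOOS assessments between the study and control group". The only regression that involves KOOS is one "to assess whether there is a relation between SIR with both MRI protocols" and the KOOS score. It relates the image measure to the questionnaire and does not compare the techniques. No baseline covariate, change score or repeated-measures model is named for KOOS.

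**The concern.** The trial collects a preoperative KOOS from each patient, but the arm comparison gives that score no stated role. In a trial this small, a baseline value that predicts the outcome is one of the few sources of extra precision available without more patients. SIR has no such value, because MRI is done only at one year; KOOS has one.

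The article says in its Conclusion that the results may clarify which technique gives the best clinical and functional outcomes, yet the sample size was set for SIR alone. The KOOS comparison is therefore imprecise from the start. At stake is the width of its confidence intervals and the size of difference it can detect.

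**Working it through.** **Inputs from the document.** 15 patients per arm after loss to follow-up, 36 in total (Sample size calculation); KOOS preoperatively and at one year (Data collection methods); two-sample test (Statistical analysis). Two-sided 5% alpha is taken, since sidedness is not stated.

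**Assumed.** The correlation ρ between preoperative and one-year KOOS is not given; a range of 0.2 to 0.6 is shown. No KOOS SD is given, so results are in SD units.

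**1. The plan's own figure.** It concerns SIR: "to detect a difference of 0.25 in SI (SD 0.21" and so on, "with a power of 90 % and an alpha of 5" per cent. By the normal approximation, n per arm = 2 × (1.960 + 1.282)² × (0.21/0.25)² = 2 × 10.51 × 0.7056 = 14.8, rounded up to 15. Then 30 × 1.2 = 36. The figure reproduces and carries no power claim for KOOS. It is used here only for the number of patients.

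**2. Unadjusted test, 15 per arm.** The standard error of the difference is √(2/15) = 0.365 SD, with 28 degrees of freedom. By the noncentral t distribution, the difference detectable with 80% power is 1.06 SD.

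**3. ANCOVA, 15 per arm.** The variance is multiplied by (1 − ρ²) × (1 + 1/(2n − 4)), where the second term, 1 + 1/26 = 1.038, is the small-sample cost of estimating the slope. There are 27 degrees of freedom. The last column is the inverse of the variance factor, less 1.

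| Assumed ρ | 1 − ρ² | With small-sample term | Detectable difference (SD) | Equivalent extra patients |
|---|---|---|---|---|
| 0.2 | 0.96 | 0.997 | 1.06 | none |
| 0.3 | 0.91 | 0.945 | 1.03 | 6% |
| 0.4 | 0.84 | 0.872 | 0.99 | 15% |
| 0.5 | 0.75 | 0.779 | 0.94 | 28% |
| 0.6 | 0.64 | 0.665 | 0.87 | 50% |

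The confidence interval is about 12% narrower at ρ = 0.5 (ratio 0.884) and unchanged at ρ = 0.2. If ρ were 0, ANCOVA would cost about 2% in width (ratio 1.021).

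**4. If nobody is lost, 18 per arm.** The detectable difference is 0.96 SD unadjusted and 0.85 SD with ANCOVA at ρ = 0.5.

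**5. If the tested value is the change score.** With equal variances at the two visits, the variance factor is 2(1 − ρ): 1.2 at ρ = 0.4, 1.0 at 0.5 and 0.8 at 0.6. Since 2(1 − ρ) − (1 − ρ²) = (1 − ρ)², which is never negative, the change score cannot beat ANCOVA except by the small-sample term. Below ρ = 0.5 it is worse than ignoring baseline.

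**The case against.** The strongest reply is that nothing here is wrong. Patients are randomised, so the two-sample test is unbiased and keeps its type I error. Chance baseline differences are already reflected in its standard error. A reader might infer that, with about 15 per arm, baseline imbalance makes the KOOS result invalid. The document does not support that; only precision is at issue.

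A reader might also infer that the plan certainly discards the preoperative score. The text does not go that far: a test on change scores fits its wording. This leaves the recommendation standing, because the change score is no more efficient than ANCOVA, as step 5 shows.

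The gain depends on a correlation the document does not give, and it disappears near 0.2. That stands, and it is why a range is shown. At ρ = 0.5 the detectable difference is still 0.94 SD, so adjustment does not make KOOS a well-powered comparison.

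It is also tempting to extend the point to KT-2000 laxity, isokinetic strength and the hop test. The document does not clearly support this. For the two visits, Data collection methods names only the physical examination recorded on the IKDC form and KOOS. The endpoint section describes those measures within the IKDC paragraph, which ends in a four-group classification, and IKDC outcomes are compared by chi-square. No continuous arm comparison of them is stated.

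Finally, the Mann–Whitney option protects against non-normality in a bounded score, and plain ANCOVA would remove that protection. This is fair, and the fix has to supply a replacement.

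**Conclusion.** The point holds as a low-cost gain in precision on a secondary outcome. The article fixes the KOOS test explicitly, so this is a comment on a stated method and not on a detail left to a fuller document.

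The size runs from nothing at ρ near 0.2 to a detectable difference of 0.87 SD in place of 1.06 SD at ρ = 0.6. It rests on the assumed correlation, two-sided 5% alpha, 80% power, 15 patients analysed per arm and a roughly linear relation between the two scores. The primary SIR analysis, the sample size and the validity of the planned KOOS test are not in question.

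**What to change.** In Statistical analysis, replace the KOOS sentence with this specification: each one-year KOOS subscale is analysed by a linear model with technique as factor and the preoperative score of the same subscale as covariate, and the adjusted difference is reported with its 95% CI. If residuals are clearly non-normal, a rank-based ANCOVA or a bootstrap interval is used in place of the plain Mann–Whitney test. This also settles which KOOS value is compared.

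The cost is two sentences and one degree of freedom per model. No extra visits, patients or software for the main model are needed, since the section already plans linear regression in SPSS. Keep the change to KOOS.
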